**Methods/design:**

Baby Smiles was a five-year, four-site randomized intervention trial with a 2 × 2 factorial design. Four hundred participants were randomly assigned to one of four treatment arms in which they received either brief Motivational Interviewing (MI) or health education (HE) delivered during pregnancy and after the baby was born. In the prenatal study phase, the interventions were designed to encourage dental utilization during pregnancy. After childbirth, the focus was to utilize dental care for the infant by age one. The two primary outcome measures were dental utilization during pregnancy or up to two months postpartum for the mother, and preventive dental utilization by 18 months of age for the child. Medicaid claims data will be used to assess the primary outcomes. Questionnaires were administered at enrollment and 3, 9 and 18 months postpartum (study end) to assess mediating and moderating factors.

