During the same period as the MI research described above, the Klamath County, Oregon (USA) Department of Public Health conducted a community-based intervention program to promote dental visits by establishing a dental home for pregnant women covered by Medicaid (Oregon Health Plan), the state- administered national program of dental health insurance for qualified, low-income individuals [23]. Women served by Medicaid in Oregon State are eligible for comprehensive dental care during their pregnancy and for two months postpartum. Pregnant women in the county program received home visits or a one-on-one session at the Women, Infants, and Child Center at the health department by a dental hygienist and were assigned a dental home under an Oregon Health Plan managed care program. Le and colleagues used structured telephone interviews to identify factors that influenced women in the program to use, or not to use, available dental services [24]. The interviews asked specifically about stress and dental-related issues within a Stages of Change conceptual model [25] to determine factors that prevented or encouraged movement toward the action of going to the dentist. Overall, 55.8% of eligible women received dental care compared to less than 9% of pregnant women statewide and stress and dental issues were related to utilization. Follow-up showed 85% of the infants of the mothers who used care were caries free at 2 years old. In a similar cohort drawn from neighboring counties that did not participate in the program, only 58.9% of 2-year olds were found to be caries free [26].

The evaluation of the Klamath County Oregon program and the two earlier trials of MI counseling about Early Childhood Caries raised unanswered questions about whether MI is more effective than traditional health education in promoting dental visits and, if MI is superior to health education, at what stage of pregnancy or early childhood would it be most effective. This study should help fill these gaps.

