#### MI: postpartum

The first postpartum session occurs at 9 months postpartum and follows the same approach as the prenatal MI intervention but with a focus on the child. An Early Childhood Caries prevention menu is used information about oral hygiene and dietary practices and the age one dental visit. Mothers are asked to identify menu items that interest them and barriers to implementing these items are identified and discussed. This session is followed by one telephone call about six weeks afterwards to identify problems with the achievement of the mother’s stated goals.

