### Study schedule

Figure 1 summarizes the flow of study procedures from a participant’s perspective. The prenatal intervention in-person session was delivered at baseline when the participant was recruited, and the postpartum intervention was delivered, in person, when the participant’s child was nine months old. Counselors debriefed about the prenatal intervention when the participant’s child was three months old. The postpartum debrief was conducted at the study end visit.

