### Study outcomes

#### Primary study outcome variable

The primary outcome measures for the study will be dental utilization during the prenatal period and up to two months postpartum for the mother, and preventive dental utilization by 18 months for the child. These data are part of the Medicaid claims database and will be obtained from the Oregon Division of Medical Assistance Programs, which is the section of the Department of Health and Human Services that administers the Oregon Medicaid claims database. The data will include all claims related to dental procedures covered under the Oregon Health Plan by Current Dental Terminology (CDT) codes. For example the OHP-defined category “Preventive Dental Services” (CDT codes - 100 s, 1000 s) includes routine and problem-based dental exams, cleanings, and fluoride treatments.

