Additionally, it is hypothesized that outcomes will be mediated by a women’s readiness to change. We will test whether changes in readiness to change over the course of the intervention mediates the effects of MI on the outcome measures for the mother at three months post-partum and for the child by 18 months of age. First, the analyses for the primary hypotheses will be used to examine whether there is an effect of the MI intervention on mother’s outcomes at three months post-partum and child outcomes by 18 months of age. Second, to demonstrate the association between the intervention and readiness to change, we will construct regression models with readiness to change as the dependent variable (e.g., change between baseline and three months post-partum for the mother’s outcomes, and change between and/or three months postpartum and 9 or 18 postpartum for the child’s outcome) and intervention and the baseline value of readiness to change as independent variables. Third, to demonstrate the association between readiness to change and the outcome after adjusting for the intervention and to demonstrate the reduction of the intervention effect on the outcome after adjusting for readiness to change, we will construct regression models with both treatment and readiness to change as independent variables and the outcome measure as the dependent variable.

To formally test the mediation effect as described in the third step above, we will use a version of the Sobel test [41], which tests whether the indirect effect of intervention on the outcome through the mediator (defined as the product of the intervention to mediator path and the mediator to outcome path) is significantly different from zero. The mediation effect is referred to as the indirect effect of intervention because it reflects the intervention effect on the outcome through the mediating variable [42]. We will use the bootstrap method of Preacher and Hayes [43] to estimate the indirect effect and bias-corrected 95% confidence interval (CI) for each individual mediator and for all the mediators as a group, based on 1,000 bootstrap samples using a Statistical Package for the Social Sciences (SPSS®; SPSS Inc., Chicago, Illinois) macro (http://www.afhayes.com/spss-sas-and-mplus-macros-and-code.html).

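### The maternal mediation analysis measures readiness to change one month after the outcome window closes, so a significant indirect effect cannot be told apart from reverse causation.

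*Protocol article*

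**What the plan says.** All of this is in the protocol article.

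- **Mother's outcome** (Primary study outcome variable): "dental utilization during the prenatal period and up to two months postpartum for the mother". The Background explains the cut-off, since women on Medicaid in Oregon are "eligible for comprehensive dental care during their pregnancy and for two months postpartum".
- **Prenatal intervention** (Study schedule): "The prenatal intervention in-person session was delivered at baseline when the participant was recruited".
- **Readiness measurements** (Abstract, Methods/design): "Questionnaires were administered at enrollment and 3, 9 and 18 months postpartum (study end) to assess mediating and moderating factors".
- **Mediator model** (Secondary aims): regressions with "readiness to change as the dependent variable (e.g., change between baseline and three months post-partum for the" mother's outcomes. Intervention and baseline readiness are the predictors. For the child, the changes named run to 9 or 18 months.
- **Outcome model** (Secondary aims): the plan will "construct regression models with both treatment and readiness to change as independent variables and the outcome measure as the dependent variable". The product of the two paths is then tested by a version of the Sobel test, with a bias-corrected bootstrap 95% interval.
- **Outcome date used for mediation** (Secondary aims): "outcome measures for the mother at three months post-partum and for the child by 18 months of age". For the mother this is not the two-month definition.
- **Postpartum intervention** (MI: postpartum): "The first postpartum session occurs at 9 months postpartum".

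The section attaches no caveat about time order to the mediation test.

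**The concern.** A mediator has to lie between the intervention and the outcome. Here the first readiness value after the prenatal session is taken when the mother's outcome is already settled. The two planned regressions see only that MI, visits and readiness are associated. They cannot distinguish readiness that led to a visit from a visit that led to higher reported readiness. The second route is plausible because the Readiness Ladder includes an action stage, which a woman might report because she has already been to the dentist.

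At stake is the stated hypothesis that readiness mediates the effect of MI. A positive test would be reported as the mechanism by which MI works, when the design cannot show this for the mother's outcome.

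**Working it through.** The plan gives no figure to reproduce on this point. The check sets the dates side by side and then asks how often reverse causation alone would produce a positive test.

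**Dates, mother.** The prenatal session is at baseline, the outcome closes at 2 months postpartum, and the next readiness value is at 3 months: 3 − 2 = 1 month after closure. The time points in Secondary aims are given as examples, but the schedule (enrollment, 3, 9, 18 months) has no other value inside the window. Taking the outcome at three months, as Secondary aims words it, does not help: readiness would be measured at the end of the window, after the visits it is meant to explain.

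**Dates, child, postpartum MI.** The session is at 9 months and the outcome closes at 18 months. The 18-month value coincides with closure. The 9-month value is taken at about the time of the session, and the article does not say which comes first. If the questionnaire comes first, postpartum MI cannot have affected it. If it comes second, it is taken before the follow-up call some six weeks later.

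**Simulation of reverse causation only.** From the article: 400 women, 200 prenatal MI (148 + 52) v 200 prenatal HE (148 + 52), and 80% retention, which gives 0.8 × 400 = 320. Assumed, because the article gives no such figures: the visit rates, and the rise δ in later readiness (in SD) caused by a visit. Readiness has no effect on visits, so true mediation is zero.

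- Mediator model: readiness change = a₀ + a·MI + a₂·baseline readiness. Estimate a, standard error sₐ.
- Outcome model: logit P(visit) = b₀ + c′·MI + b·readiness change. Estimate b, standard error s_b. Version A fits this as written in the article (2,000 trials per setting); version B adds baseline readiness (1,000 trials per setting).
- Sobel z = ab / √(a²s_b² + b²sₐ²), significant if |z| > 1.96. Version B also uses a 95% Monte Carlo product interval in place of the planned bootstrap, which was not run.

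Percentage of trials declaring mediation (version B: Sobel / Monte Carlo):

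| δ (SD) | A: 45 v 61%, n=400 | B: 45 v 60%, n=400 | B: 40 v 60%, n=400 | B: 40 v 60%, n=320 |
|---|---|---|---|---|
| 0 | 0.0 | 0.0 / 0.1 | 0.0 / 0.0 | 0.0 / 0.0 |
| 0.3 | 2.5 | 2.5 / 5.8 | 4.1 / 10.2 | 1.9 / 7.3 |
| 0.5 | 9.0 | 8.4 / 12.4 | 16.0 / 21.0 | 10.9 / 14.9 |
| 0.8 | 23.1 | 21.4 / 24.3 | 36.7 / 38.7 | 30.9 / 34.3 |
| 1.0 | 34.2 | 29.9 / 30.9 | 49.6 / 51.1 | 40.1 / 43.6 |

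When MI does not change visits (50% v 50%), the rate is at most 4.7% by Sobel and 5.9% by the Monte Carlo interval.

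**Hand check of one cell** (δ = 1.0, 40% v 60%, n = 400). The false a-path is δ × (0.60 − 0.40) = 0.20. In version B the residual variance of readiness given baseline is 0.75, and visits add δ² × 0.4 × 0.6 = 0.24, so the SD is √0.99 = 0.995. The standard error is 0.995 × √(1/200 + 1/200) = 0.0995, and 0.20 / 0.0995 = 2.01, just above 1.96. A rate near one half is therefore expected, as found.

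**The case against.** The strongest reply is that this is a secondary analysis. The three primary contrasts compare randomized groups on claims data and do not involve readiness, so the trial's answer on MI v HE does not depend on this point. That stands, and it limits how much the point matters.

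The size of the problem also rests on inputs the article does not contain. At a 0.3 SD shift the Sobel rate is below 5%, and excess false mediation needs both that MI raises visits and that visits raise readiness. The plan's first step examines the former. The latter depends on a ladder modified for this study whose items and scoring are not shown, so the mechanism is plausible but not established. That also stands. None of it restores the time order.

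Three stronger readings are tempting but not supported:

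- A reader might infer that the test will report mediation whenever MI works. Even in the most adverse setting tabulated, about half of the trials do not.
- A reader might infer that no usable readiness value exists for postpartum MI and the child. The 18-month value is clearly unsuitable, but for the 9-month value the article only leaves the order unstated.
- A reader might infer that omitting baseline readiness from the outcome model is a separate error. It may be shorthand in a condensed article, and no consequence is shown: at nearly the same visit rates, the results with and without it are similar.

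**Conclusion.** The point holds for the mother's outcome. On the published schedule, no readiness value after the prenatal session precedes the close of the two-month window, so the planned test cannot support the stated mediation hypothesis. This follows from the dates alone. Readiness at 18 months has the same flaw for the child outcome.

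The size is conditional. With assumed visit rates of 40–45% v 60–61%, an assumed shift of 0.3 to 1.0 SD and 400 women, the Sobel test declares false mediation in about 2.5% to 50% of trials. At 320 women and 40% v 60% the range is about 2% to 40%. It is zero by Sobel if visits do not move readiness. Adding baseline readiness to the outcome model does not remove the false signal.

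The article also contradicts itself on the date of the mother's outcome: two months in the outcome definition, three months in the mediation text. The primary contrasts are unaffected.

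**What to change.** 1. Report the relation between readiness and the mother's dental utilization as an association, not as mediation. Do the same for postpartum MI with 18-month readiness.
2. Reconcile the three-month date for the mother's outcome in Secondary aims with the two-month definition used elsewhere.
3. State whether the 9-month questionnaire comes before or after the postpartum session.
4. Keep formal mediation for the sequence the schedule supports: prenatal MI v HE (Group 1 v Group 3), readiness at 3 or 9 months, then child preventive claims dated after that questionnaire. Include baseline readiness in both models.

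Items 1 to 3 change wording only, but the maternal mediation hypothesis becomes descriptive. Item 4 is more than wording: that mediation analysis drops any child claims dated before the questionnaire, so its outcome is narrower than utilization by 18 months. The primary child outcome stays as defined. Item 4 also rests on 148 + 148 = 296 women, or about 0.8 × 296 ≈ 237 with questionnaires at the expected overall retention. Correct time order is necessary for a mediation claim but does not by itself rule out other common causes of readiness and child visits.

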### Primary outcome analysis

The analysis strategy for the primary hypotheses will involve intent-to-treat analyses, where women and their children will be compared according to their randomly- assigned intervention group regardless of whether, or how much of the intervention they actually received. The only exception to the intent-to-treat rule is in our analysis for child utilization of preventive dental care; this will be limited to only live-born children (*e*.*g*., miscarriages and stillborn will be excluded). Information about fetal loss will be collected by telephone interviews by the counselors with the participants because information about miscarriages is not on the state official birth record.

Intervention effects will be tested using the three *a priori* group contrasts described previously. Separate logistic regression analyses will be used to test each contrast using a significance level of 0.016.

A preliminary step in the analysis will be to check if the women in the four intervention groups are comparable on baseline values of prior dental utilization and important predictors of dental utilization (*e*.*g*. Readiness Ladder status, oral health quality of life). If an imbalance is found between the groups, additional covariates will be included in the logistic regression analyses to adjust for baseline differences. The primary independent variable in the regression analyses will be an indicator variable for intervention group. In addition, indicator variables for county and counselor will be included in all regression models to account for the stratification of the randomization by county and counselor.

Descriptive summaries will be produced for all the primary outcomes (mother and child dental utilization) by intervention group averaged over the four study counties, as well as by county, to assess the similarity of the observed intervention effects across the different counties. Formal testing for differences in the intervention effect among counties is possible by testing for interactions between county and intervention group in the regression analyses described below. However, we do not expect the intervention effects to differ vastly among the counties, and the sample size has not been selected to test for such county differences.

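### The readiness-to-outcome model in the mediation analysis leaves out baseline readiness, so a change-score mediator can hide real mediation or give a spurious negative indirect effect

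*Protocol article*

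**What the plan says.** The mediation plan is in the protocol article under Secondary aims. The aim is worded in terms of change: "We will test whether changes in readiness to change over the course of the intervention mediates the effects of MI on the outcome measures". The three steps are:

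- Step one takes the MI effect on the outcome from the primary analyses.
- Step two models readiness, for example "change between baseline and three months post-partum for the mother’s outcomes", with "intervention and the baseline value of readiness to change as independent variables".
- Step three supplies the readiness-to-outcome path: "we will construct regression models with both treatment and readiness to change as independent variables and the outcome measure as the dependent variable".

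The formal test then "tests whether the indirect effect of intervention on the outcome through the mediator" differs from zero, with the indirect effect "defined as the product of the intervention to mediator path and the mediator to outcome path". The interval is a "bias-corrected 95% confidence interval (CI) for each individual mediator and for all the mediators as a group, based on 1,000 bootstrap samples".

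Under Primary outcome analysis, the article checks whether the groups are "comparable on baseline values of prior dental utilization and important predictors of dental utilization". Readiness Ladder status is its first example of such a predictor. Baseline covariates are added there only if the groups turn out to be imbalanced.

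**The concern.** Randomization protects the path from intervention to readiness. It does not protect the path from readiness to utilization, which is an observational association within each arm. It is confounded by anything that affects both later readiness and utilization, even when the arms are perfectly balanced. Baseline readiness is the obvious such variable, and the article itself says that it predicts utilization. The check for baseline imbalance therefore does not deal with the problem.

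The mediator makes matters worse. Women who start high have less room to rise and tend to regress toward the mean, so change is negatively correlated with baseline. Without the baseline in the model, the coefficient of change mixes the effect of becoming more ready with the opposite-signed effect of having started less ready.

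At stake is the one mediation hypothesis that the article spells out step by step. It could be rejected, or appear with the wrong sign, because of where the mothers started and not because of what MI changed.

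**Working it through.** The plan states no figure for the mediation test, so there is none to reproduce.

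**Inputs from the article.** Table 1 gives 148 + 52 + 148 + 52 = 400 women. The prenatal contrast is 200 v 200 and the postpartum contrast 296 v 104. Missing data expects 80% retention, and readiness comes from questionnaires, so n = 0.80 × 400 = 320. The outcome is binary utilization, analysed by logistic regression.

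**Assumptions, not in the documents.** Readiness is in SD units. MI raises follow-up readiness by a = 0.4 SD. The baseline to follow-up correlation is ρ = 0.5. Utilization is about 50%. The log OR per SD is b for follow-up readiness and g for baseline readiness.

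**Model.** Baseline B has SD 1. Follow-up is F = ρB + aT + √(1 − ρ²)·e, the log odds of utilization are gB + bF (centred), and the mediator is M = F − B.

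**Expected coefficient of M without baseline.** Within an arm:

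- Var(M) = 2(1 − ρ) = 1 and Cov(B, M) = ρ − 1 = −0.5.
- The slope of B on M is −(1 − ρ)/[2(1 − ρ)] = −1/2, whatever ρ is.
- Since F = B + M, the slope of F on M is 1 − 1/2 = 1/2.
- The coefficient of M is therefore about b/2 − g/2 = (b − g)/2.

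**With baseline added.** gB + bF = (g + b)B + bM, so the coefficient of M is b. Entering F in place of M also gives b.

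**Numbers.**

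- Real mediation, b = 0.4, g = 0: 0.4/2 = 0.20 instead of 0.40. The indirect effect is 0.4 × 0.20 = 0.08 instead of 0.4 × 0.40 = 0.16.
- No readiness effect, b = 0, g = 0.4: −0.4/2 = −0.20 instead of 0. The indirect effect is 0.4 × (−0.20) = −0.08 instead of 0.
- b = g = 0.4: (0.4 − 0.4)/2 = 0. The two cancel exactly, so this is an extreme case.

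Simulation agrees: in the first case the mean coefficient was about 0.20 as written and 0.41 with baseline added.

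**Rejection rates.** Path a comes from linear regression of M on treatment and baseline. Path b comes from logistic regression with and without baseline. The Sobel statistic is z = ab/√(a²·SE_b² + b²·SE_a²), two-sided 5%, change score as mediator, n = 320 at 1:1 unless stated.

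| Setting | As written | Baseline added |
|---|---|---|
| Real mediation, b = 0.4, g = 0 | about 28% power | about 72% power |
| No effect, b = 0, g = 0.4 | about 28%, all negative | about 2% |
| Same, MI effect 0.2 SD | about 6% | not inflated |
| Same as row 2, allocation 237:83 | about 22% | not inflated |
| No effect, b = 0, g = 0 | not inflated | not inflated |

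At 400 women, power in the first row is 39% v 87%, and false rejection in the second is about 40% v 2–4%.

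The bias-corrected bootstrap behaves the same way. With a = ρ = g = 0.5 and no readiness effect at n = 320, it rejected about 59% as written and about 9% with baseline added. This used only 120 trials of 400 resamples, so it is rough.

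**The case against.** **The lists may not be complete.** Neither step-two nor step-three wording mentions the county and counselor indicators, which the article requires in all regression models. The article is condensed, and it says that the full protocol is posted elsewhere. Step three might therefore contain baseline readiness without saying so. This stands as a reason not to read the omission as deliberate. But the article names baseline readiness in one model and not in the next, in the same paragraph, and no other section supplies it.

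**Falsely confirmed mediation.** A reader might infer that the plan is prone to declare mediation in the hypothesised direction when there is none. The article does not support that. It defines the mediator as change, and the false rejections are then all negative. A negative indirect effect would not be taken as support for the hypothesis. Only if step three meant the follow-up level would the bias run upward, and the wording disfavours that reading.

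**Step one may filter.** If a significant MI effect on utilization were required first, false rejections would be far fewer when MI has no effect at all: about 0.5% jointly at 400 women. The article does not make step one a gate. A gate would also not restore the power lost when mediation is real.

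**The size depends on the assumptions.** This stands. The false-rejection rate depends strongly on the MI effect on readiness, which is unknown. In addition, mothers' readiness is measured at three months postpartum while their utilization is counted to two months postpartum. A model in which later readiness drives utilization therefore fits the child's outcome better than the mother's, and the rates should not be carried over to the mother's analysis as they are.

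**Conclusion.** The point holds. As stated, the third-step model omits a variable that the second step includes and that the article regards as predictive of the outcome. With change as the mediator, the path coefficient is pulled from b to about (b − g)/2. The consequence is missed mediation or a spurious negative indirect effect.

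The rates are illustrations under assumed paths. False rejection needs both that MI moves readiness, which the trial hypothesises, and that baseline readiness predicts utilization, which the article presumes. The loss of power with a change score needs no separate baseline effect. The direction of the bias follows from the algebra, given similar spread of readiness at the two times and higher readiness going with more utilization.

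This concerns a secondary, mechanistic analysis. A reader might infer that the trial's main conclusions are at risk. They are not: the three primary contrasts do not use these models.

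**What to change.** State that the third-step model includes the same baseline (or pre-interval) readiness value as the second step, and that the Sobel and bootstrap indirect-effect estimates use it too, entered as a covariate in the mediation macro. Change and follow-up level then give the same readiness-to-outcome coefficient, so it no longer matters which of them step three means.

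No new data are needed, because the value is already collected and already used in step two. The cost is a somewhat larger standard error for that path. If the follow-up level were used and baseline had no separate effect, adjustment would lower power from about 93% to 86% at 400 women under the assumptions above. Further baseline predictors, such as prior dental utilization or oral health quality of life, are optional and not part of this correction.

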### Sample size

The sample size is 400 women with 80 to 120 women enrolled within any one county.

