### Analysis

Three *a priori* group contrasts will be used to test the primary hypotheses regarding intervention effects on the use of dental services (see Table 1 for a summary of the 4 study groups):

(1) Groups 1 and 2 (MI Prenatal) versus Groups 3 and 4 (HE Prenatal) will test the hypothesis that the MI intervention results in a greater frequency of utilization of dental care by the woman during pregnancy.

(2) Groups 1 and 3 (MI Postpartum) versus Groups 2 and 4 (HE Postpartum) tests the hypothesis that the MI intervention results in a greater frequency of utilization of preventive dental care by the children during the first 18 months of life.

(3) Group 1 (MI Prenatal and Postpartum) versus Group 3 (MI Postpartum only) will test the hypothesis combination of MI delivered during pregnancy and postpartum will result in a greater frequency of preventive dental care for children during the first 18 months of life.

A significance level of 0.016 was used in the sample size and power calculations for the primary hypotheses to take into account the three comparisons to be performed. The study will also provide some evidence for the effect of MI during pregnancy, without MI postpartum, on child utilization. However, the study is not powered to demonstrate this effect, which will likely be modest in the absence of intervention postpartum.

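### The formal test of mediation is a Sobel test, which is conservative in its usual form, although a bootstrap interval for the same indirect effect is already planned

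*Protocol article*

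**What the plan says.** Under Secondary aims, the Protocol article sets out regression steps for mediation and then turns to inference on the indirect effect. For the formal test, "we will use a version of the Sobel test". The quantity tested is "defined as the product of the intervention to mediator path and the mediator to outcome path", compared with zero.

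The same paragraph then brings in a bootstrap method "to estimate the indirect effect and bias-corrected 95% confidence interval (CI) for each individual mediator and for all the mediators as a group". The number of resamples is set at 1,000. Testing is thus given to the Sobel procedure, and estimation with an interval to the bootstrap, for one and the same quantity.

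No significance level is attached to the mediation test. The only stated level belongs elsewhere: "A significance level of 0.016 was used in the sample size and power calculations for the primary hypotheses" (Analysis). No path size, mediator standard deviation or power is given for mediation.

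**The concern.** The usual Sobel test divides the product of two estimated coefficients by a delta-method standard error and refers the ratio to a normal distribution. A product of two estimates is skewed unless at least one path is estimated very precisely. The test then rejects too seldom under the null and loses power under the alternative. A bootstrap interval does not rely on that normal approximation.

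A 95% interval that excludes zero is itself a verdict on the null hypothesis of the Sobel test, so readers will see two verdicts. Taken literally, the less sensitive procedure decides. At stake is the trial's stated mechanism, mediation by readiness to change: it could be declared unsupported while the planned interval for it excludes zero.

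**Working it through.** **There is no figure in the plan to reproduce.** The article gives no power or effect size for mediation, so the check is a simulation under stated assumptions.

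**Inputs from the Protocol article**
- N = 400 (Sample size).
- Retention of 80% (Missing data). Readiness comes from questionnaires, so about 0.80 × 400 = 320 women would have the mediator.
- Allocation (Table 1): prenatal 148 + 52 = 200 v 200, or 50:50; postpartum 148 + 148 = 296 v 52 + 52 = 104, or 74:26.
- Binary outcome with logistic regression (Primary outcome analysis).
- 1,000 bootstrap samples (Secondary aims).

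**Assumed, because not given**
- Two-sided 5% for both procedures.
- Continuous mediator with path a in SD units and path b in log-odds per SD.
- Intercept rate 0.5 and direct effect 0.2 log-odds.
- The Sobel test is the normal-theory form.

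**Why the test is conservative.** The statistic is z_S = ab / √(a²·SE_b² + b²·SE_a²). Dividing through by SE_a·SE_b gives z_S = z_a·z_b / √(z_a² + z_b²), which is always smaller in size than the weaker of the two path statistics. With equal paths it is z/√2, so each path must reach 1.96 × √2 = 2.77 before the Sobel test is significant. Two paths each at z = 2.5 are individually significant, yet z_S = 2.5/√2 = 1.77.

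**Longer simulation runs, 50:50 allocation** (rejection rates in %; BC = bias-corrected bootstrap)

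| N | a, b | Replicates | Sobel | Percentile | BC | Percentile minus Sobel | Sobel and BC differ |
|---|---|---|---|---|---|---|---|
| 320 | 0, 0.4 (null) | 1,500 | 1.6 | 4.7 | 6.9 | 3.1 | 5.3 |
| 320 | 0.35, 0.35 | 1,200 | 54.2 | 75.0 | 81.0 | 20.8 | 26.8 |
| 400 | 0.35, 0.35 | 1,000 | 71.3 | 87.4 | 91.7 | 16.1 | 20.4 |
| 320 | 0.3, 0.6 | 1,000 | 68.2 | 78.1 | 81.1 | 9.9 | 13.1 |

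In these runs the Sobel test was significant with the BC interval covering zero in at most 0.1% of trials. The disagreement therefore runs almost wholly one way.

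**Shorter runs (200 replicates per cell), percentile minus Sobel**
- a = b = 0.3: N = 320, 50.5 − 29.5 = 21.0 points (50:50) and 45.5 − 24.0 = 21.5 (74:26); N = 400, 69.0 − 49.5 = 19.5 (50:50) and 61.0 − 42.0 = 19.0 (74:26).
- a = b = 0.35, 74:26: N = 320, 64.0 − 38.0 = 26.0; N = 400, 79.0 − 67.5 = 11.5.
- a = b = 0.5: N = 400, 0 (50:50) and 99.0 − 97.5 = 1.5 (74:26); N = 320, 1.0 (50:50) and 94.0 − 90.5 = 3.5 (74:26).

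These cells are rough. At N = 400, 50:50, a = b = 0.35, the short run gave 87.5 − 77.5 = 10.0 points, against 16.1 in the longer run. Against the BC interval, the gaps over all non-null cells ran from 0 to 38 points.

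**Separate repeat.** Sobel, percentile and BC gave 57, 73 and 80% at N = 320, a = b = 0.35; 45, 70 and 79% with 74:26 allocation; and 1.6, 4.4 and 6.4% in the null case.

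**Size of the BC interval.** The Monte Carlo standard error of 6.9% on 1,500 replicates is √(0.069 × 0.931/1,500) = 0.65 points. The excess over 5% is therefore about 1.9/0.65 = 2.9 standard errors. Part of the BC interval's apparent gain comes from this excess, so the percentile interval is the fairer comparator.

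**Number of resamples.** For a percentile endpoint, the Monte Carlo SD in standard-error units is √(0.025 × 0.975/B)/φ(1.96), which is 0.084 for B = 1,000 and 0.027 for B = 10,000. One thousand is usable.

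**The case against.** The strongest reply is that the article gives the two procedures different roles: the Sobel test decides and the bootstrap describes. That stands. A reader might infer a flat contradiction, or an open choice between two tests after the results are known, but the text supports neither. What remains is that the deciding role goes to the less sensitive procedure, with nothing said about a split result.

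Second, the wording is a version of the Sobel test, and the cited source is not at hand. The bootstrap that follows could be that version, which would leave only one procedure. The text does not say so, and the point is therefore conditional on the normal-theory form. If the bootstrap was meant, the same edit makes that plain.

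Third, a reader might infer a fixed loss, such as 12 to 20 points. The documents do not support any single figure, because they give none of the quantities it depends on. The loss is close to nil when both paths are strong.

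Fourth, a conservative test for a secondary mechanism claim is defensible, and the error is towards claiming too little. This is fair and limits the weight of the point. It does not explain choosing a test whose size is near 1.6% when a percentile interval held about 4.4 to 4.7% in the same null case.

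Finally, the number of resamples and the seed are details for an analysis plan or code, and no finding is made on them.

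**Conclusion.** The point holds in a limited form. The article makes a Sobel test the formal test of an indirect effect for which it also plans a bootstrap interval. If that test is the normal-theory one, it is conservative, and the two procedures can give different verdicts: 13 to 27% of simulated trials in the three non-null longer runs, comparing Sobel with the planned bias-corrected interval.

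At two-sided 5% and N = 320 to 400, the power lost is about 0 to 2 points when both paths are strong (a = b = 0.5), rising to 3.5 (percentile) or 6.5 (bias-corrected, 97.0 − 90.5) in the one cell with N = 320 and 74:26 allocation. Against a percentile bootstrap it is roughly 15 to 25 points when both paths are moderate (0.3 to 0.35); single short runs fell between 10 and 26. With a = 0, b = 0.4 and N = 320, the size is near 1.6% for Sobel and 6 to 7% for the bias-corrected interval. The planned interval is therefore not a clean replacement as it stands.

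All of these figures rest on assumed paths, outcome rate and significance level. The consequence is confined to a secondary aim; the three primary contrasts at 0.016 are untouched.

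**What to change.** In the mediation paragraph of Secondary aims, drop the Sobel test as the formal test. State that mediation is claimed only if the percentile bootstrap 95% confidence interval for the indirect effect excludes zero. Change the interval type from bias-corrected to percentile in the same place. If the phrase about a version of the Sobel test was meant to denote the bootstrap, say so. More than 1,000 resamples is optional.

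The cost is a sentence or two of text and trivial computing. The statistical price is a less conservative test: in the null case examined, the rejection rate rises from about 1.6% to about 4.4 to 4.7%, still within the nominal 5%. The change should be recorded before the mediation analysis is run.
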